**Blinding**

Because of the odor and color of traditional Chinese medicine decoction, the patients and clinical therapists will be unblinded in this trial. But the outcome assessors and data analysts will be blinded throughout the entire study.

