**Abstract**

**Introduction:** The outbreak of a novel coronavirus (SARS-CoV-2) and associated COVID-19 disease in late December 2019 has led to a global pandemic. It directly leads to high morbidity and mortality, but also results in a devastating effect on the global economy. Nowadays many trials are underway on this disease to evaluate the efficacy of various therapeutic remedies. This study aims at investigating the effect of Traditional Chinese Medicine, maxingshigan-weijing for treating patients with COVID-19.

**Methods and analysis:** This is an open-label, multicenter randomized controlled clinical trial. One hundred and forty patients infected by SARS-CoV-2 will be randomly assigned to the control group or the experimental group ( Traditional Chinese Medicine, TCM group ) in an equal ratio. The patients in control group will receive routine supportive clinically care including the therapies of anti-viral, anti-bacterial and ameliorating the related symptoms, while patients in TCM group will be asked to take traditional Chinese medicine, maxingshigan-weijing for consecutive 14 days in addition to supportive care. All data will be gathered at baseline and on days 3, 7, 10 and 14. The primary outcome measure will be the number of days till at least one of the clinical symptoms (fever, cough, malaise, shortness of breath) improves in the first 14 days of treatment. Secondary outcome measures will include TCM Syndrome Scoring System and the time of negative of SARS-CoV-2 nucleic acid. A laboratory test will be taken before and after treatment to assess the safety of TCM.

**Discussion:** The study may help to identify the the efficacy and safety of Traditional Chinese Medicine, Maxingshigan-weijing in treating COVID-2019.

**Trial registration:** Chinese Clinical Trial Registry, ChiCTR2000030759. Registered on March 13th 2020, <http://www.chictr.org.cn/.>

**Keywords:** SARS-CoV-2, COVID-2019, Traditional Chinese Medicine ( TCM ), Maxingshigan-weijing decoction, Randomized controlled trial, Protocol

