**METHODS**

**Study design**

This is an open-label, multicenter, randomized controlled, comprehensive treatment clinical study, with outcome assessors and data analysts blinded to the group assignment. Eligible participants with Mild and Moderate Pneumonia caused by SARS-CoV-2 will be randomly assigned to either the experimental ( Traditional Chinese Medicine + Routine supportive care ) or the control group ( Routine supportive care ) in an equal proportion. Routine supportive care remains the major treatment, including the therapies of anti-viral, anti-bacterial and ameliorating the related symptoms[21]. The study consisted of three phases: a screening period, a treatment period of 14 days, and a follow-up period of 2 weeks. Fig. 1 briefly shows the study flow chart, and Fig. 2 enumerates the treatment schedule and outcome measures. The study adheres to the Standard Protocol Items: Recommendations for Intervention Trials (SPIRIT 2013) checklist [22].

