***Secondary outcomes***

**TCM Syndrome Scoring System**

### TCM Syndrome Scoring System will be used at the baseline and day 3, day 7, day 10 and day 14 of the drug intervention. It is a checklist covering 4 main, 7 secondary and 13 accompanying items. These items are the symptoms and signs summarized by experts according to the clinical manifestations of COVID-2019[24]. The main items consisting of fever, coughing, fatigue and short breath use a four-point scale (0, 2, 4 and 6) depending on the severity; the 7 secondary items including dysphoria, diarrhea, pharyngalgia, expectoration, muscular soreness, nasal obstruction and rhinorrhoea use 0-3-point scale; the 13 accompanying items contain chest pain, headache, aversion to cold, dizziness, nausea and vomiting, anorexia, abdominal distension, dry mouth, anxiety, spontaneous sweating, insomnia, wheezing and blood tinged sputum, and each item is rated on 0-1 scale ( 0 stands for asymptomatic, 1 stands for symptomatic ). The total scores sum up to a range from 0 to 58, with higher scores indicating more severe levels of disease.

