**Rate of symptom recovery**

The rate of symptom (fever, cough, malaise, shortness of breath) recovery will be one of the secondary endpoints. Fever denoted the subaxillary temperature being 37 degrees or greater. The cough and malaise was self-reported by the patients. Recovery of symptoms will be defined as the complete resolution of fever, cough, malaise, shortness of breath.

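### The unqualified claim of blinded outcome assessment does not protect outcomes built on symptoms that unblinded patients report themselves

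*Protocol*

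**What the plan says.** Three statements in the protocol bear on this point.

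- **Who is blinded.** Study design describes an open-label trial "with outcome assessors and data analysts blinded to the group assignment". The Blinding section explains that, because of the decoction's smell and colour, "the patients and clinical therapists will be unblinded in this trial", and then adds "But the outcome assessors and data analysts will be blinded throughout the entire study". Neither section limits the assessor claim to particular outcomes.
- **Who supplies the symptom data.** Under Rate of symptom recovery: "The cough and malaise was self-reported by the patients". The same section defines the endpoint: "Recovery of symptoms will be defined as the complete resolution of fever, cough, malaise, shortness of breath".
- **Where those symptoms enter the primary outcome.** The Abstract counts the days until "at least one of the clinical symptoms (fever, cough, malaise, shortness of breath) improves in the first 14 days of treatment". Sample size uses the same any-symptom event. Primary Outcome, under Measurements, uses fever alone, judged by temperature below 37 °C.

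The TCM Syndrome Scoring System section lists 24 items with a maximum of 58 points and does not say who scores them. The chest imaging section is the only outcome section that names a specific blinded assessor, a radiologist.

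**The concern.** For a self-reported symptom, the judgement that it has improved is the patient's. A blinded member of staff may write the answer down, but the answer has already been formed by someone who knows whether they are taking the decoction. The control arm receives routine care with no placebo, so an expectation effect would probably make relief look earlier or more frequent in the TCM arm. That is also the direction of the one-sided hypothesis in Sample size.

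The any-symptom primary is the more exposed of the two versions. It needs only one of four symptoms to improve, so a single report of less cough or less malaise is enough. A reader who takes the blinding statement at face value would discount reporting bias for outcomes that have no protection against it.

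**Working it through.** **1. Which outcomes the claim can cover**

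| Outcome | Source of the judgement in the protocol | Does assessor blinding protect it? |
|---|---|---|
| Cough, malaise | Patient self-report (stated) | No |
| Symptom recovery (all four symptoms resolved) | Includes cough and malaise | No, for those two components |
| Primary as in Abstract and Sample size | Any one of four symptoms | No, when cough or malaise triggers the event |
| Primary as in Primary Outcome | Temperature | It can |
| RT-PCR, laboratory tests, ECG | Measured | It can |
| Chest imaging | Blinded radiologist (stated) | Yes |
| Shortness of breath | Not stated | Open |
| TCM score | Rater not stated | Depends on the item (step 2) |

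**2. Share of the TCM score that may be patient-reported**

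The stated maximum reproduces: 4 × 6 + 7 × 3 + 13 × 1 = 24 + 21 + 13 = 58.

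The protocol does not classify items by source, so the sorting below is an assumption.

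- Cough and fatigue only, taking fatigue as the malaise called self-reported elsewhere: 6 + 6 = 12; 12/58 = 21%.
- Adding dysphoria, sore throat and muscle soreness (3 × 3 = 9) and ten one-point items (all except spontaneous sweating, wheezing and blood-tinged sputum): 12 + 9 + 10 = 31; 31/58 = 53%.
- Adding shortness of breath (6) and nasal obstruction (3): 31 + 9 = 40; 40/58 = 69%.

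**3. Illustration for a yes/no recovery endpoint**

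Inputs: 70 per arm and 10% dropout (Randomization, Sample size), so 70 × 0.9 = 63 analysed per arm. Assumed, because the protocol gives no figure: no true effect, true recovery of 40% to 60%, and a reporting shift of 5 or 10 percentage points in the TCM arm. For a two-category outcome, the Wilcoxon test planned for secondary outcomes is essentially a comparison of two proportions.

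Formula: z = (p1 − p0) / √{[p0(1 − p0) + p1(1 − p1)]/63}. One-sided rejection is P(Z > 1.645 − z). Two-sided rejection is P(Z > 1.96 − z) + P(Z < −1.96 − z).

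| p0 → p1 | SE | z | One-sided 5% | Two-sided 5% |
|---|---|---|---|---|
| 0.60 → 0.65 | 0.0861 | 0.58 | 0.14 | 0.09 |
| 0.40 → 0.45 | 0.0880 | 0.57 | 0.14 | 0.09 |
| 0.60 → 0.70 | 0.0845 | 1.18 | 0.32 | 0.22 |
| 0.40 → 0.50 | 0.0882 | 1.13 | 0.30 | 0.21 |

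**4. A separate illustration on the time-to-event scale**

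Sample size assumes a ratio of 1.5, one-sided 5% and 70% power. The required number of events is 4 × (1.645 + 0.524)² / (ln 1.5)² ≈ 115. With exponential medians of 3 and 4.5 days, about 92% have an event by day 14, so 115/(2 × 0.922) ≈ 62 per arm, close to the stated 61.

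Suppose expectation alone raised the rate of reported improvement by 10% or 20%. Then z = ln(1.1) × √115 / 2 = 0.51 or z = ln(1.2) × √115 / 2 = 0.98, and the one-sided false-positive rate is about 13% or 25%. These hazard shifts are also assumed. Where measured fever is the symptom that triggers the event, the shift would be smaller.

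**The case against.** The strongest reply is that the protocol is open about its design. It calls itself open-label repeatedly and says that patients are unblinded in the sentence before the assessor claim. If outcome assessors means the staff who rate and record, the two statements do not collide literally. That much stands: nothing is concealed, and the fault is a claim without limits rather than a false one. It does not remove the problem, because blinding the recorder leaves the patient's judgement unblinded.

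Four stronger readings are tempting, and the documents do not support them.

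- **That the TCM score is patient-reported.** The protocol names no rater. Only 12 of 58 points can be linked to a self-report statement, and that statement concerns another outcome. The rest is inference from the nature of the items.
- **That blinding can hold only for temperature, PCR and imaging.** Vomiting, wheezing, rhinorrhoea and blood-tinged sputum can be observed by staff, laboratory and ECG measures can be read blind, and shortness of breath is not said to be self-reported.
- **That the false-positive rates measure the bias in this trial.** The shifts are assumed. Recovery also requires fever, which is measured, to resolve, so over-reporting on cough and malaise cannot turn a febrile patient into a recovered one.
- **That the results will be presented as blinded.** Nothing in the protocol says so.

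**Conclusion.** The point holds in a limited form. The unqualified blinding statements in Study design and Blinding do not protect the symptom-recovery endpoint, or the any-symptom primary outcome of the Abstract and Sample size. This follows from the text, given that a self-reported symptom is assessed by the patient. For TCM score items that only the patient can report, it follows by inference; depending on how items are sorted, they carry about 21% to 69% of the maximum score.

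The illustrated inflation of a one-sided 5% error, to about 14% or 30-32%, shows that a modest reporting shift is enough to matter for a yes/no secondary endpoint. It is neither an estimate for this trial nor one for the log-rank primary.

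The consequence depends on which primary outcome is in force. Under the fever-only definition, the exposed outcomes are secondary. Under the any-symptom definition, the main conclusion is exposed as well. The open-label design itself is not at fault, and the point does not reach temperature, RT-PCR, the blinded imaging reading, or laboratory and ECG measures.

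**What to change.** 1. In Study design and Blinding, limit the assessor claim to outcomes that a blinded person actually determines, for example temperature, RT-PCR, imaging, laboratory and ECG measures, and say who determines each.
2. Label cough, malaise, symptom recovery and the patient-reported TCM items as open-label patient-reported outcomes. State who rates the TCM score and which items come from the patient.
3. State that efficacy will not be concluded from these outcomes alone.
4. Reconcile the primary outcome in the Abstract and Sample size with the measured-temperature definition under Primary Outcome.
5. Re-justify the 3-day median and the 1.5 ratio for fever. Sample size states them for the any-symptom event, and the inclusion criteria do not require fever at entry, so the number of patients with a fever event to observe has to be addressed.

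Steps 1 to 3 need only wording; the price is that the symptom outcomes carry less weight in the conclusion. Steps 4 and 5 cost more, because the sample-size assumptions must be restated and the planned 140 patients may no longer match the stated 70% power. Recruitment had begun before this protocol version, so the change should be dated and made without sight of outcomes by arm.

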**Prohibition and permission for concomitant treatment**

All concomitant care and interventions are permitted other than concomitant receipt of any other experimental treatment.

**Patient and public involvement**

Patients in this study will not be involved in the design, recruitment or conduction of the study, but they will be informed of the Clinical examination results they had accepted.

**INTERVENTIONS**

Maxingshigan-weijing decoction consists of 10 g of Herba Ephedra (Mahuang), 10 g of Amygdalus Communis Vas (Xingren), 45 g of Gypsum Fibrosum (Shigao), 30 g of Rhizoma phragmitis (Lugen), 20 g of Peach kernel (Taoren), 20 g of Winter Melon kernel (Dongguaren), 30 g of Trichosanthes Kirilowii Maxim (Gualou), 12 g of Pericarpium Citri Reticulatae (Chenpi), 12 g of Rhizoma Pinelliae (Jiangbanxia), 12 g of caulis bambusae in taeniis (Zhuru), 30 g of semen lepidii (Tingliz), 15 g of semen lepidii (Shichangpu), 10 g of curcuma zedoary (ezhu) and 5 g of Radix Glycyrrhizae (Gancao). Maxingshigan-weijing decoction will be prepared by TCM pharmacy of the First Affiliated Hospital of Wenzhou Medical University.

Inpatients will be randomly assigned to two groups receiving either Routine supportive care alone which includes Stay in bed, Nasal cannula of oxygen therapy, broad-spectum antibiotics and antivirals, or the combination of Maxingshigan-weijing decoction for continuous 14 days, 200 mL twice a day at 10 AM and 4PM. All participants will be hospitalized so that they could be quarantined and closely observed. What is more, to ensure compliance with the medication, patients will be asked to return the empty wrapping papers. If there will be any remaining medicine, it will be recorded.

**MEASUREMENTS**

***Primary Outcome***

The primary outcome will be the number of days until the clinical symptom of fever improves in the first 14 days of treatment following randomisation. Fever will be defined as an improvement when the temperature is less than 37℃.

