**Sample size**

Based on previous clinical practice of using TCM fought against SARS and H1N1 influenza patients [23], it is estimated the median survival time in the TCM group as 3 days, and 1.5 times longer in the control group. Concerning the analysis of the primary endpoint, the duration of time before improvement of at least one of the common cold-like symptoms (fever, cough, malaise, shortness of breath) , will be estimated using the Kaplan-Meier method, and

the survival curves will be compared between groups using the log-rank test. And this study is designed to detect a statistically significant difference with a level of 5% and a power of 70% (one-sided type-1 error of
[figure not shown]
 =5%，
[figure not shown]
 =30%), so approximately 61 participants in each group will be needed. Thus, under the prediction of a dropout rate of 10%, the sample size of 140 participants will be sufficient to detect a clinically important difference in this trial.

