**Coronavirus nucleic acid test**

The coronavirus nucleic acid test by reverse transcription polymerase chain reaction ( RT-PCR ) will be conducted at the baseline and day 3, day 7, day 10 and day 14 of the study intervention. The time ( in days ) of the respiratory tract sample and blood specimens SARS-CoV2 RT-PCR to be negative for two consecutive times based on the first testing time will be defined as primary outcome.

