**Trial status**

The trial protocol is Version 2.0, October 14, 2020. Recruitment began March, 2020, and is anticipated to be completed by December 31, 2020.

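### The protocol gives conflicting primary outcomes (fever alone, or any one of four symptoms), and the sample size belongs to the four-symptom endpoint, not to the one defined under Primary Outcome

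*Protocol*

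**What the plan says.** Four places in the protocol assign or imply the primary outcome.

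- **Measurements, Primary Outcome:** the definition reads "The primary outcome will be the number of days until the clinical symptom of fever improves in the first 14 days of treatment". Improvement means a temperature below 37℃.
- **Abstract:** "the number of days till at least one of the clinical symptoms (fever, cough, malaise, shortness of breath) improves", also over the first 14 days.
- **Sample size:** the primary endpoint is "the duration of time before improvement of at least one of the common cold-like symptoms", with the same four symptoms listed. The planning medians, the 61 per group, the 70% power and the total of 140 are given for this event.
- **Secondary outcomes, Coronavirus nucleic acid test:** the time to two consecutive negative RT-PCR results, "based on the first testing time will be defined as primary outcome". The Abstract puts the same quantity among the secondary measures: "Secondary outcome measures will include TCM Syndrome Scoring System and the time of negative of SARS-CoV-2 nucleic acid".

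The Statistical Analysis section assigns a log-rank test to the primary outcome without saying which event that is. The protocol gives no hierarchy, co-primary status or multiplicity rule. On timing, Trial status says: "The trial protocol is Version 2.0, October 14, 2020. Recruitment began March, 2020".

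**The concern.** Time to fever improvement and time to the first improvement in any of four symptoms are different events. A patient with fever and cough could have an event on day 2 under one definition and on day 6 under the other. The Inclusion criteria do not require fever: a mild case needs only mild clinical symptoms. A patient without fever can contribute to the four-symptom endpoint but already meets the below-37℃ criterion on day 0.

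Two things are at stake. First, the planned test is fixed but the event it is applied to is not, so the text leaves room to settle the primary result after data exist. Patients and therapists know the allocation, and cough and malaise are self-reported, so the choice should not be left open. Second, the stated 70% power is a statement about the four-symptom endpoint. It cannot be carried over to the endpoint defined under Primary Outcome.

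**Working it through.** **1. Reproduce the plan's sample size.** Inputs from the Sample size section: median 3 days with TCM and 1.5 times that, 4.5 days, in control; one-sided 5%; power 70%; 10% dropout. Allocation is 1:1 (Randomization) and follow-up is 14 days (Primary Outcome). Exponential times are my assumption, giving a hazard ratio of 1.5.

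- Schoenfeld: events = 4(1.645 + 0.524)² / (ln 1.5)² = 115 after rounding up.
- Freedman: events = [(1 + 0.667)/(1 − 0.667)]² × (1.645 + 0.524)² = 118, or 59 per arm if every patient has an event.
- Event probability by day 14: TCM 1 − 2^(−14/3) = 0.961; control 1 − 2^(−14/4.5) = 0.884; mean 0.922.
- Schoenfeld with 14-day censoring: 115 / 0.922 / 2 = 62.3 per arm.

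The stated 61 lies between 59 and 62.3. For dropout, 61/0.90 rounds up to 68 per arm, 136 in total, which 140 covers. Reading the control median as 7.5 days (3 plus 1.5 times 3) would need only about 23 events and does not give 61, so 4.5 days is the reading the plan used.

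**2. Set the candidates side by side.**

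| Place | Event labelled primary | Sample size planned for it? |
|---|---|---|
| Abstract; Sample size | First improvement in any of four symptoms | Yes |
| Measurements, Primary Outcome | Fever below 37℃ | No |
| Nucleic acid test (under Secondary outcomes) | Two consecutive negative PCR tests | No; the Abstract calls it secondary |

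The first two are real rivals. The third contradicts both its own heading and the Abstract.

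**3. False-positive risk if the better of two were reported.** With two independent tests at one-sided 5%, the risk is 1 − 0.95² = 9.75%. With perfect correlation it is 5%. Fever is one of the four symptoms, and in a febrile patient the four-symptom time can never exceed the fever time. The two are therefore positively correlated and the risk lies between these limits.

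**4. Power if fever is primary (illustration).** The protocol gives no planning median for fever and no febrile share at entry. I keep the hazard ratio of 1.5, one-sided 5% and the mean event probability of 0.922, take 140 × 0.90 = 126 evaluable patients, and count only patients febrile at baseline as informative. The febrile share is an assumption.

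Power = Φ(√(E/4) × ln 1.5 − 1.645), with E = 126 × share × 0.922.

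| Assumed febrile share | Events E | Power | Total N to keep 122 evaluable febrile patients (122 / share / 0.90) |
|---|---|---|---|
| 100% | 116.2 | 71% | 136 |
| 80% | 93.0 | 62% | 170 |
| 60% | 69.7 | 52% | 226 |
| 40% | 46.5 | 40% | 339 |

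**The case against.** The strongest reply is that the damage is limited. One log-rank test is planned, not several. Outcome assessors and data analysts are blinded, and the sample size arithmetic is sound. All of that is true. Blinding limits a results-driven choice but does not remove it, and a fixed test does not help while its event is undefined.

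A reader might infer more than the text supports:

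- **Three equal primaries and a 14.3% error rate** (1 − 0.95³). This needs three independent candidates. The PCR label sits under Secondary outcomes and conflicts with the Abstract, so it is most likely a drafting slip, and the two real candidates are correlated.
- **A sample size for an endpoint the Methods do not use.** The Sample size section is itself under Methods and calls the four-symptom event primary. The Methods contradict themselves; they do not adopt fever throughout.
- **An endpoint changed during recruitment.** Version 2.0 is dated seven months after recruitment began, but the previous version is not at hand and nothing in the text shows a change.
- **Fever as the obvious choice because it is measured by thermometer.** Symptom-relieving therapy is part of routine care and nearly all concomitant treatment is permitted, so unblinded clinicians can influence temperature. The afebrile patients at entry are a further difficulty.

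**Conclusion.** The contradiction is real and should be resolved before analysis. Fever alone and any one of four symptoms are both called primary, and the analysis section does not say which is tested. The PCR label needs correcting but is a minor part, and the point stands without it.

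The 9.75% ceiling is conditional: it applies only if both candidates were tested and the better one reported, and it assumes independence. It is not the error rate of the plan as written. The stated 70% power belongs to the four-symptom endpoint. For fever it cannot be confirmed from the protocol, and the range of about 71% down to 40% rests on assumed febrile shares of 100% to 40% and on a hazard ratio borrowed from the other endpoint. Neither 61 nor 140 is miscalculated.

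**What to change.** Name one primary outcome and use it in the Abstract, Sample size, Primary Outcome and Statistical Analysis sections. It should be the one fixed before the first patient was enrolled, which the sponsor can establish from its own records. State the date of the choice and that it was made without by-arm data. Make the other endpoint secondary, and change the end of the nucleic acid test section so that it reads as a secondary outcome.

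- **If the four-symptom endpoint is kept:** correct the Primary Outcome section, including what counts as improvement for each symptom. The Sample size figures then stand.
- **If fever is kept:** correct the Abstract and Sample size sections, define the primary analysis set as patients febrile at baseline, and restate the power with an explicit febrile share and planning medians for fever.

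The cost is an amendment to the wording. If fever is chosen, there is also a less favourable stated power, or more patients if the sponsor wants to restore it.

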**Inclusion criteria**

1. Participants are 18-85 years of age, either male or female.
2. Diagnosed as positive for severe acute respiratory syndrome coronavirus 2 (SARS-CoV-2)
3. Symptomatic. Mild (mild clinical symptoms without signs of pneumonia in chest X-ray), and Moderate (fever or [respiratory](../../../../C:/Users/[name]/Downloads/%25E6%259C%2589%25E9%2581%2593/Dict/8.9.0.0/resultui/html/index.html" \l "/javascript:;) [symptom](../../../../C:/Users/[name]/Downloads/%25E6%259C%2589%25E9%2581%2593/Dict/8.9.0.0/resultui/html/index.html" \l "/javascript:;) with signs of pneumonia in chest X-ray) .
4. Signed the informed consent before treatment.
5. Agreed not to enroll in any other clinical trials.
6. Inpatients

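### A single temperature below 37℃ is enough for a permanent primary event, because the fever endpoint asks for no repeat or sustained reading; the likely result is diluted power and a time to improvement that is too short

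*Protocol*

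**What the plan says.** The Primary Outcome section counts days to improvement of fever "in the first 14 days of treatment following randomisation" and gives the event rule as "Fever will be defined as an improvement when the temperature is less than 37℃". It states no number of readings, minimum duration, time of day or handling of relapse. Under Rate of symptom recovery, the protocol adds: "Fever denoted the subaxillary temperature being 37 degrees or greater".

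The Statistical Analysis section compares the arms with a log-rank test. On timing, the Abstract says "All data will be gathered at baseline and on days 3, 7, 10 and 14". Fig. 2 shows the same days for symptom relief and lists no separate temperature readings.

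Confirmation does appear for another outcome. Under Coronavirus nucleic acid test, RT-PCR has "to be negative for two consecutive times based on the first testing time".

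**The concern.** A time-to-event analysis takes the first qualifying observation and ignores what follows. Take a participant at 37.2℃ on entry, 36.9℃ at one later reading and 38.5℃ at the next. That participant has a primary event dated to the 36.9℃ reading.

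Such false events happen in both arms while fever is still present. The arm that stays febrile longer has more time in which to collect them, so the two curves are drawn together. At stake are the power of the comparison, planned at only 70% one-sided, and the reported number of days to improvement, which comes out too short. The point concerns only participants who are febrile at baseline, and it does not depend on use of antipyretics.

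**Working it through.** **1. The plan's own sample size.** Inputs from Sample size: medians of 3 days (TCM) and 1.5 × 3 = 4.5 days (control), so a hazard ratio of 1.5; one-sided 5%; 70% power.
- Schoenfeld events: 4 × (1.645 + 0.524)² / (ln 1.5)² ≈ 115.
- Exponential event probabilities by day 14: 1 − 0.5^(14/3) = 0.961 and 1 − 0.5^(14/4.5) = 0.884, mean 0.922.
- 115 / 0.922 = 124.7, or about 62 to 63 per arm, against the stated 61.
- 122 / 0.9 = 136 after rounding up, against the stated 140.

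The arithmetic reproduces and is not at issue.

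**2. Chance of a false low reading.** Assumptions, since the protocol gives no variability: a still-febrile patient has mean temperature μ, normal within-patient SD σ of 0.3 or 0.5℃, and independent readings. Then p = Φ((37 − μ)/σ) per reading, and the chance of at least one false low in k readings is 1 − (1 − p)^k. Here k = 4 for days 3/7/10/14 and k = 14 for daily readings, in a patient febrile throughout.

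**3. Power.** Simulated trials with 61 febrile patients per arm, exponential resolution with medians 3 and 4.5 days, readings N(μ, σ) while febrile and N(36.5, 0.25) afterwards, and log-rank z > 1.645. With true resolution observed, power is about 0.67 on the visit schedule and 0.70 daily. The Monte Carlo standard error at 1,000 trials is √(0.5 × 0.5/1000) ≈ 0.016, so differences of two or three points mean little.

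| μ | σ | p | ≥1 false low, 4 visits | ≥1 false low, daily | Power, single reading, visits | Power, single reading, daily |
|---|---|---|---|---|---|---|
| 37.5 | 0.3 | 0.048 | 18% | 50% | 0.61 | 0.52 |
| 37.5 | 0.5 | 0.159 | 50% | 91% | 0.50 | 0.30 |
| 37.8 | 0.3 | 0.004 | 2% | 5% | 0.68 | 0.68 |
| 37.8 | 0.5 | 0.055 | 20% | 55% | 0.62 | 0.52 |
| 38.0 | 0.3 | <0.001 | 0.2% | 0.6% | 0.67 | 0.69 |
| 38.0 | 0.5 | 0.023 | 9% | 28% | 0.63 | between 0.54 and 0.70 |

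The last cell was not read from a run of its own. It lies between the daily results for p = 0.05 (0.54) and p = 0 (0.70).

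**4. Time to improvement.** With daily readings, μ = 37.5 and σ = 0.5, the apparent medians are about 2.2 and 2.6 days, against 3.5 and 5.0 for true resolution on the same daily grid.

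**5. Effect of confirmation.** Requiring two consecutive daily readings below 37℃ gives power of about 0.59 to 0.68 at means of 37.5 to 37.8. Two consecutive false lows over 14 days occur in 3% (σ = 0.3) to 26% (σ = 0.5) of patients who stay at 37.5℃, against 50% to 91% with one reading. Confirming only across scheduled visits gives 0.58 to 0.63, against 0.50 to 0.68 for a single reading: a gain in the noisiest setting and a loss where noise is low.

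**6. Sensitivity.** With readings correlated within patient (0.5), daily, σ = 0.5, single-reading power is 0.41 (μ = 37.5) and 0.54 (μ = 37.8); with confirmation it is 0.60 and 0.63. The conclusion does not rest on independence.

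**The case against.** **It may be left to the SAP.** The Primary Outcome section does not say one reading, and a SAP, not shown here, could set how a daily value is derived. That is fair, and the single-reading rule is an inference from silence. But the section states a complete operative rule that one reading satisfies. A SAP that asked for more would be changing the primary event.

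**The two cut-offs coincide.** A reader might infer that fever at 37℃ or above and improvement below 37℃ is itself an error. It is not: the two are consistent complements, and the fix below keeps the same line.

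**Power falls to 30%.** A reader might take this as the general result. The documents do not support it. That figure needs daily readings, which the protocol does not schedule, with low-grade fever and the larger SD. On the stated visits the loss is nearly nil at σ = 0.3 with means of 37.8℃ or above. Moreover, the 70% in Sample size is stated for improvement in at least one of four symptoms, not for fever, and fever is not required at entry, so 61 febrile patients per arm is an illustration.

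**False positive findings.** A reader might infer that the rule favours the TCM arm. Noise common to both arms dilutes a true difference and does not by itself inflate type I error. Returning fever can also still show in the TCM Syndrome score, although that score does not correct the primary result.

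**Conclusion.** The concern stands as a weakness in the definition of the primary event: in participants febrile at baseline, one transient reading below 37℃ counts for good. Under the stated assumptions, the loss on the day 3/7/10/14 schedule runs from nothing to about 17 points of power (0.67 to 0.50). With daily readings it runs from nearly nothing to about 40 points (0.70 to 0.30). It is material when fevers are low-grade or readings are frequent and noisy. It is small on the visit schedule at 38℃ or above.

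The direction follows from the text. The size rests on an assumed SD and fever level that the protocol does not give. This is a cheap improvement worth making, because planned power leaves no reserve; it does not invalidate the design.

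**What to change.** First reconcile the primary outcome. The Abstract and Sample size use improvement in at least one of four symptoms, Primary Outcome uses fever alone, and Coronavirus nucleic acid test also labels RT-PCR negativity as primary.

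Then, in Primary Outcome, keep the protocol's own 37℃ line and define the event as the first day on which the subaxillary temperature is below 37℃ and remains so at every recorded reading through the following day. Date it to the first of these days. State that a low reading followed within that span by one of 37℃ or above is not an event. Name the daily inpatient readings to be used and add them to Fig. 2, which does not list them. Do not confirm across scheduled visits only.

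The cost is protocol wording and the collection of daily temperatures from participants who are already hospitalised. The protocol does not say that daily charts exist, so this has to be confirmed, also for those already enrolled, since recruitment began in March 2020. The event is known one day later. A first fall on day 14 needs a day-15 reading, which is not scheduled, or is censored. Where several readings are taken each day, an occasional reading of 37℃ or above after resolution will delay some events.
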